#### Secondary outcomes

The time to reach the protein target will be defined as the number of days from the beginning of the administration of EN to the day at which at least 80% of the planned protein administration has occurred. The trial investigator will estimate that day by analyzing the medical records.

GRVs, episodes of vomiting, the number and volume of diarrhea stools, and the need for postpyloric nutrition will be documented in the medical records and entered in the eCRF by the trial investigator. Diarrhea will be defined as passing of loose stools three or more times per day. The number and volume of stools will be documented in the medical records. Volumes of diarrhea stools exceeding 1 L/day will be reported.

Aspiration of EN is defined as the presence of EN in the airway of the patient. It will be assessed by a nurse during standard airway care and documented in the medical records. The number of aspiration episodes and the incidence of VAP will be entered in the eCRF by the study investigator. Total serum protein, albumin, and prealbumin concentrations on days 1 and 5 will be obtained from the electronic medical records and entered in the eCRF by the study investigator. The ICU and hospital length of stay will be entered in the eCRF by the study investigator after analysis of the medical records. The information on whether the patient is alive or dead on day 28 will be obtained by telephone.

### Plans to promote participant retention and complete follow-up {18b}

After a participant is enrolled or randomized, the study site will make every reasonable effort to follow the participant for the entire study period. Study site staff members will be responsible for developing and implementing local standard operating procedures to achieve maximal follow-up.

### Data management {19}

The study data will be entered online in an Internet-based database and collected from medical records. The study staff members will have access to the medical records of the patients. Investigators will be responsible for (1) screening of patients, (2) obtaining informed consent, (3) randomization, and (4) collecting study data and entering the data in the eCRF. The statistician will analyze the study data in cooperation with the principal investigator. The data will be stored for 15 years after completion of the study and then destroyed.

To promote data quality, the eCRFs of each participant will be reviewed by another member of the study team.

### Confidentiality {27}

All study-related information will be stored securely at the study site. All participant information will be stored in locked file cabinets in areas with limited access. All local databases will be secured with password-protected access systems. Forms, lists, logbooks, appointment books, and any other listings that link participant ID numbers to additional identifying information will be stored in a separate locked file in an area with limited access.

### Plans for collection, laboratory evaluation, and storage of biological specimens for genetic or molecular analysis in this trial/future use {33}

Not applicable.

In this study, no biological specimens for genetic or molecular analysis will be collected.

## Statistical methods

### Statistical methods for primary and secondary outcomes {20a}

For analyses of study data, the intention-to-treat principle will be used.

For analyses of the primary outcome, the Kaplan-Meier curve, log-rank, or Wilcoxon test will be used. Standard descriptive statistics (i.e., number of available values, mean, SD, median, 25% and 75% quartiles, minimum and maximum) will be calculated for continuous variables. Categorical variables will be described by using tables of frequency. Secondary outcome measures will be compared between study groups with the *t* test or Mann-Whitney test as applicable, and the chi-square test will be used for categorical data. Differences in laboratory tests between different days of measurement will be analyzed with paired tests (paired *t* test or non-parametric Wilcoxon test). A Kaplan-Meier curve will be used to demonstrate 28-day mortality. A significance level of 5% will be used for all statistical tests. Confidence intervals will be presented as appropriate.

The data analyses will be performed after completion of the study. Interim analysis is not planned.

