### Outcomes {12}

The primary outcome of the trial is the time from the beginning of the administration of EN to the time at which at least 80% of the target energy is delivered. This will be reported as the day of EN administration. The Kaplan-Meier time-to-event analysis will be used for the analysis of the primary outcome.

Secondary outcomes:
Time from the beginning of the administration of EN to the time at which at least 80% of the target protein dose is delivered. This will be reported as the day of EN administration. The Kaplan-Meier time-to-event method of analysis will be used for the analysis of this secondary outcome.Achievement of the energetic target. This outcome will be aggregated as the proportion of patients who achieve the energetic target during the study period.Tolerance of EN GRV will be aggregated as the proportion with GRV < 250 mL, 250–500 mL, and > 500 mL. Episodes of vomiting will be aggregated as the proportion of patients with any number of episodes of vomiting. Diarrhea stools will be aggregated as the proportion of patients with diarrhea stool > 1 L/day. The need for postpyloric nutrition will be aggregated as the proportion of patients with this need.Incidence of complications of EN. The number of aspiration episodes will be aggregated as the proportion of patients with any number of episodes of aspiration. VAP will be aggregated as the proportion of patients with confirmed VAP.Total serum protein, albumin, and prealbumin concentrations on days 1 and 5. Serum concentrations of protein, albumin, and prealbumin will be aggregated as the mean.ICU and hospital length of stay. ICU and hospital length of stay will be aggregated as the mean. The day of admission and day of discharge will be counted as 1 day.The 28-day mortality will be evaluated with a Kaplan-Meier curve.

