### Sample size {14}

Studies focused on the primary target of our study are lacking. However, we have identified several studies comparing bolus and continuous administration of enteral feeding. These studies included small numbers of patients, were conducted in different patient populations, and did not assess the time to reach the nutritional targets as a primary outcome. However, for calculation of the sample size, we hypothesized a difference of 1 day between groups (target being reached on day 2 and day 3, respectively). The alpha was set to 5%, and the power was set to 80%. The estimated sample size was 122 patients per arm. To account for potential drop-out, we increased the sample size to 300 participants in total, with 150 patients in each study arm.

**Table 3 Tab3:** Participant timeline

	Study period							Follow-up
Time point	Screening	D0	D1	D2	D3	D4	D5	D28
Number of visits	1	2	3	4	5	6	7	8
Eligibility criteria	x							
Informed consent	x							
Allocation	x							
Demographic data		x						
APACHE II		x						
SOFA score		x						
Laboratory tests (total serum protein, albumin, prealbumin)		x					x	
Estimation of energy and protein target		x						
Administration of enteral nutrition			x	x	x	x	x	
Assessment of tolerance (diarrhea, vomiting, GRV, postpyloric nutrition)			x	x	x	x	x	
Assessment of complications			x	x	x	x	x	
Assessment of energetic and protein targets			x	x	x	x	x	
Assessment of hospital LOS, ICU LOS, and mortality								x

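### The primary test is left open between the log-rank and an unspecified Wilcoxon test; one test should be fixed before the data are seen, preferably stratified by the Table 1 BMI class

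*Protocol article*

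**What the plan says.** The statistical methods section {20a} names the primary analysis in one sentence: "For analyses of the primary outcome, the Kaplan-Meier curve, log-rank, or Wilcoxon test will be used". No order, condition or rule follows, although the secondary comparisons in the same paragraph at least carry a qualifier about applicability. The outcomes section {12} adds only "The Kaplan-Meier time-to-event analysis will be used for the analysis of the primary outcome", which names an estimator and not a test. It also fixes the scale of the outcome: "This will be reported as the day of EN administration".

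Section {20a} sets the error level: "A significance level of 5% will be used for all statistical tests". The sample size section {14} uses a 5% alpha and 80% power, and for the effect states "we hypothesized a difference of 1 day between groups (target being reached on day 2 and day 3, respectively". It concludes "The estimated sample size was 122 patients per arm", and then, for drop-out, "we increased the sample size to 300 participants in total, with 150 patients in each study arm".

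Table 1 sets the energy target at 25-30 kcal/kg of actual body weight below BMI 30 and at 11-14 kcal/kg for BMI 30-50. The intervention description {11a} gives starting amounts and increments for each arm that do not depend on BMI. Patients with BMI 18-50 are eligible {10}. The trial design section {8} names no stratification factor, and section {20b} plans no additional analysis.

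**The concern.** Two tests for one primary hypothesis, with no rule, leave room to choose after the results are known. The 5% level then holds only if the choice is in fact made beforehand. The trial is not blinded {17a}, and analysis follows completion of the study.

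The word Wilcoxon is itself unclear. Section {20a} also uses it for the paired comparison of laboratory values, and uses Mann-Whitney for the two-sample comparison. For the primary outcome it could mean a censored-data (Gehan) test or a plain rank-sum test. Section {12} foresees patients who never reach the target, and a rank-sum test has no standard way to handle them.

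A second, smaller matter is efficiency. A patient's energy target depends strongly on the Table 1 BMI class, and the feeding steps do not. BMI class should therefore help to explain the day on which 80% of target is reached, and a test that ignores it may lose power.

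**Working it through.** **1. The planned size.** The protocol gives no SD, distribution or event rate, so 122 per arm cannot be derived from its inputs alone.

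- As a comparison of two means with a 1-day difference, it implies SD = sqrt(122 / (2 × 7.849)) = 2.79 days, where 7.849 = (1.960 + 0.842)².
- As a log-rank test with exponential medians of 2 and 3 days (assumption), HR = 3/2 = 1.5. Schoenfeld events = 4 × 7.849 / (ln 1.5)² = 191. Freedman events = 7.849 × (2.5/0.5)² = 197, rounded up.
- Mean event fraction by day 5 = [(1 − 2^(−5/2)) + (1 − 2^(−5/3))] / 2 = (0.823 + 0.685) / 2 = 0.754. This gives 127 (Schoenfeld) or 131 (Freedman) per arm. With 6 days the figures are 118 and 122; with 7 days, 112 and 115.
- Power at 122 per arm and 5 days: events = 244 × 0.754 = 184; sqrt(184/4) × 0.4055 − 1.960 = 0.79, i.e. 78.5%. At 150 per arm: events = 226; sqrt(226/4) × 0.4055 − 1.960 = 1.09, i.e. 86%.

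The exponential log-rank reading is close enough to the plan to serve as the basis for what follows.

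**2. Type I error of an open choice.** Null trials were simulated with exponential times rounded up to whole days, two-sided 5% tests, 122 or 150 per arm, medians 2 to 3 days, censoring at day 5 or 7, and 40,000 trials per setting. Log-rank or Gehan-Wilcoxon alone rejected in 4.9-5.3%. Rejection if either was significant: 6.3-7.3%. The two statistics correlate 0.91-0.96, which keeps the rise modest.

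**3. Power of the two tests.** For medians 2 v 3 days, 5-day censoring and 12,000 trials per setting, the log-rank has about 78% and the Gehan-Wilcoxon about 73% at 122 per arm, and about 86% v 82% at 150.

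**4. BMI class and the target.** Per kg, the ratio of the classes is 11/25 = 0.44 to 14/30 = 0.47. At 1.75 m (height² = 3.0625), and assuming 1 kcal/mL, one 25 mL/h step over 18 h delivers 450 kcal. Steps needed = 0.8 × target / 450, rounded up.

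| BMI | Weight (kg) | Target (kcal/day) | Steps to 80% |
|---|---|---|---|
| 20 | 61.3 | 1531-1838 | 3-4 |
| 29.9 | 91.6 | 2289-2747 | 5 |
| 30.0 | 91.9 | 1011-1286 | 2-3 |
| 45 | 137.8 | 1516-1929 | 3-4 |

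Under full tolerance, continuous feeding stepped every 4 h reaches 80% on day 1 for targets up to about 1250 kcal and on day 2 from 1400 kcal. Stepped every 8 h, it is day 2 up to 2000 kcal and day 3 from 2250 kcal. For boluses raised at every second feed, targets from 1150 to 2500 kcal all fall on day 2. BMI class can therefore move the day by as much as the 1-day effect sought, but not in every setting.

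**5. Stratified v unstratified log-rank.** Treatment HR 1.5 within BMI class, overall control median 3 days, 122 per arm, 5 days. Both the share with BMI 30 or more and the BMI hazard ratio are assumptions. Power in %, unstratified / stratified:

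| BMI hazard ratio | 15% with BMI ≥ 30 | 30% | 40% |
|---|---|---|---|
| 1.0 | 78.5 / 78.1 | 77.8 / 77.7 | 78.8 / 78.8 |
| 1.5 | 77.5 / 77.8 | 76.5 / 77.5 | 76.5 / 78.0 |
| 2 | 74.4 / 76.8 | 73.4 / 77.2 | 72.5 / 77.1 |
| 3 | 70.5 / 75.7 | 65.4 / 75.5 | 62.9 / 75.3 |

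At 150 per arm, over BMI hazard ratios 1.5-3, power is 72-85% unstratified and 84-86% stratified. With no treatment effect, a 30% share and BMI hazard ratio 2 or 3, the unstratified log-rank rejects in 5.0%.

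**The case against.** The strongest reply is that section {20a} does not say both tests will be run and the better one reported. If one test is fixed beforehand, perhaps in an analysis plan not shown, the inflation is zero. That stands, and the 6.3-7.3% is conditional on choosing by result. It does not rescue the sentence, which addresses the primary test and leaves it open. The trial is also called explorative {8}, but it sets a 5% level and 80% power for this comparison.

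A reader might infer that the Wilcoxon test in particular breaks the power claim. At 122 per arm the log-rank also falls just short of 80%, and at 150 both exceed it. Exponential times imply proportional hazards, which favours the log-rank; an effect concentrated early could narrow or reverse the gap.

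A reader might also infer that an unstratified test is wrong. It is not: it keeps its 5% level and matches a randomization with no named stratification factor. Nor does BMI class generally mean a twofold difference in target. That contrast belongs to the threshold, and BMI 20 and BMI 45 need about the same number of steps. Finally, section {17a} says the statisticians' data are pseudonymized; it does not say whether arm labels are visible, so no claim can rest on that.

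**Conclusion.** The open choice of primary test is a real but modest defect. Chosen by result, it raises the type I error from 5% to about 6.3-7.3%; fixed beforehand, it costs nothing. The power difference of about 5 points in favour of the log-rank rests on exponential medians of 2 v 3 days and 5-day follow-up.

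Stratifying by BMI class is an improvement in efficiency, not the correction of an error. The expected gain is about 0-1 point at a BMI hazard ratio of 1.5, 2-5 points at 2 and 5-12 points at 3, for shares of 15-40% with BMI 30 or more. The protocol gives neither the share nor the strength of the effect, so confidence is high on the open test and only moderate on the power loss.

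**What to change.** Before the data are seen, replace the sentence in {20a} with one primary test: the two-sided log-rank test at 5%, stratified by Table 1 BMI class (<30 v 30 or more). Report the stratified hazard ratio with its 95% confidence interval, and state how ties are handled, since the outcome is in whole days. List the unstratified log-rank and the Gehan-Wilcoxon test, named as such, as sensitivity analyses that do not decide the primary conclusion. If an analysis plan already fixes one test, bring the protocol into line with it.

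The cost is about one sentence. Height and weight are measured on admission and BMI is an entry criterion, so no new data are needed. If BMI turns out not to be prognostic, stratifying costs at most about 0.4 points of power in the simulations above.

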
## Objectives {7}

The primary study objective is to compare continuous and intermittent modes of application of enteral feeding on the time to reach an energetic target in critically ill adult patients.

Key secondary objectives are to determine the effects of the mode of administration of enteral feeding on the time to reach the protein target, the gastrointestinal tolerance (on the basis of assessment of GRV), vomiting, diarrhea, and the need for postpyloric nutrition. Other secondary objectives are complications of enteral feeding, as assessed by the incidence of aspiration and ventilator-associated pneumonia (VAP).

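### The planned arm comparison of total protein, albumin and prealbumin does not adjust for baseline, and the day 1 to day 5 change is tested only within patients; ANCOVA would use both measurements at little cost

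*Protocol article*

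**What the plan says.** Outcomes {12} lists as a secondary outcome "Total serum protein, albumin, and prealbumin concentrations on days 1 and 5" and gives the summary measure: "Serum concentrations of protein, albumin, and prealbumin will be aggregated as the mean". Change from baseline is not named as the outcome.

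Statistical methods {20a} contains two sentences that bear on these markers. The general one is "Secondary outcome measures will be compared between study groups with the *t* test or Mann-Whitney test as applicable". The specific one is "Differences in laboratory tests between different days of measurement will be analyzed with paired tests", with a paired t test or a Wilcoxon test as the options. The same section adds "A significance level of 5% will be used for all statistical tests", so the paired tests are inferential as written. No baseline covariate is mentioned, and the section on additional analyses {20b} says that none are planned.

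The article gives two times for the first sample. Outcomes {12} and the secondary-outcome part of section {18a} say day 1. In Table 3, the row that begins "Laboratory tests (total serum protein, albumin, prealbumin" is marked at D0 and D5, while enteral nutrition is marked from D1.

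**The concern.** The trial asks a between-arm question: "Key secondary objectives are to determine the effects of the mode of administration of enteral feeding". Each marker is measured twice in each patient, so the natural analysis compares the arms at day 5 while allowing for where each patient started. The plan splits this into two analyses, and neither does the whole job. The paired tests use both measurements but do not compare the arms. The t or Mann-Whitney test compares the arms, but nothing says that it takes account of the first measurement.

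At stake is precision. A modest difference between feeding modes in these markers could be missed, or estimated with a wider interval than the data require, although the measurement needed to sharpen it is already being collected.

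**Working it through.** **1. The plan's own figure.** There is none for these markers: no SD, effect size or correlation. The 122 patients per arm (150 after the drop-out allowance) in Sample size {14} belong to the time-to-target outcome. They cannot be rebuilt from the stated inputs without adding an SD or an event-time model. This point does not depend on them; they serve below only as illustrative group sizes.

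**2. What each planned test estimates.**
- Paired test: the mean of day 5 minus baseline within patients. It contains no arm contrast.
- t or Mann-Whitney test: a contrast between arms in an unadjusted quantity. Because the summary is the mean concentration, the likeliest reading is the day-5 concentration. A change score is possible but is not stated.

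**3. Variance of the arm difference.** Assume the same SD σ on both days, correlation ρ between baseline and day 5, and n patients per arm:
- day-5 values alone: 2σ²/n
- change scores: 2(1−ρ) × 2σ²/n
- ANCOVA: (1−ρ²) × 2σ²/n (large-sample form)

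So ANCOVA relative to day 5 is 1−ρ². Relative to change it is (1−ρ²)/[2(1−ρ)] = (1+ρ)/2, a cut of (1−ρ)/2.

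| ρ (assumed) | ANCOVA / day 5 | Cut | Change / day 5 | ANCOVA / change | Cut |
|---|---|---|---|---|---|
| 0.3 | 0.91 | 9% | 1.40 | 0.65 | 35% |
| 0.5 | 0.75 | 25% | 1.00 | 0.75 | 25% |
| 0.6 | 0.64 | 36% | 0.80 | 0.80 | 20% |
| 0.7 | 0.51 | 49% | 0.60 | 0.85 | 15% |
| 0.8 | 0.36 | 64% | 0.40 | 0.90 | 10% |

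At ρ = 0.7, 1/0.51 = 1.96: the same precision from day-5 values alone would need about twice the sample.

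**4. What this means for detectable differences.** Take 5% two-sided (sidedness is not stated, so this is an assumption) and 80% power. The detectable difference in SD units is (1.960 + 0.842) × √(2 × ratio / n).

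| Analysis | n = 122 per arm | n = 150 per arm | Power for an assumed 0.3 SD difference, n = 122 |
|---|---|---|---|
| Day-5 values alone | 0.359 | 0.323 | 65% |
| ANCOVA, ρ = 0.3 | 0.342 | 0.309 | 69% |
| ANCOVA, ρ = 0.5 | 0.311 | 0.280 | 77% |
| ANCOVA, ρ = 0.6 | 0.287 | 0.259 | 83% |
| ANCOVA, ρ = 0.7 | 0.256 | 0.231 | 91% |
| ANCOVA, ρ = 0.8 | 0.215 | 0.194 | 97% |

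**5. Baseline timing.** ANCOVA needs a covariate that the feeding mode cannot have influenced. A D0 sample precedes feeding, which Table 3 starts on D1. A day-1 sample may precede or follow the start of feeding. The article supports both readings, so the covariate is not yet fixed.

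**The case against.** **The arms are compared.** A reader who sees only the sentence on paired tests might infer that these markers have no between-arm test. The documents do not support that. The sentence just before it compares secondary outcomes between study groups, and Outcomes {12} makes the markers one of them. The paired test is an additional within-patient analysis.

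**No false claim of a mode effect is planned.** A reader might also infer that paired tests will be run in each arm and their p-values set against each other. That would be a poor comparison. In a simulation with no arm difference (122 per arm, ρ = 0.6), exactly one arm was significant in 9.8% of runs with no common change, and in 42.8% with a common change of 0.2 SD. The between-arm t test was significant in about 5%. But the article does not say that the paired tests are run by arm or that their results are contrasted. This is a misuse to guard against, not one that the plan commits to.

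**An unadjusted test is valid under randomization, and covariates are often left to the analysis plan.** The first part stands: this is not an invalid analysis. The second carries less weight here, because the article is not silent. It names the tests, and the point is that a better one is available for the same data.

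**The size of the gain is assumed.** This stands. The article gives no correlation, and at 0.3 the gain over day-5 values is only 9%. If the planned t test were applied to change scores, baseline would already be used in part, and the relevant figures would be those in the last column of the variance table.

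**The markers are minor.** They appear in neither the key nor the other secondary objectives in section {7}, and the trial is described as explorative. This stands and limits the weight of the point.

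**Conclusion.** The point holds as a cheap improvement. The stated between-arm test for total protein, albumin and prealbumin is valid but unadjusted, and the change over time is tested only by a method that does not compare the arms. A baseline-adjusted comparison is more precise than day-5 values alone for any non-zero correlation, and in large samples never less precise than change scores.

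For correlations of 0.3 to 0.8 the variance reduction against day-5 values runs from 9% to 64%. Against change scores it is 25% at 0.5 and 10% at 0.8. These figures assume equal SDs on the two days, a roughly linear relation and a baseline taken before feeding. They do not account for day-5 values missing through death or discharge. No primary conclusion depends on this.

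**What to change.** 1. Reconcile the time of the first laboratory sample between Outcomes {12} and section {18a} (day 1) and Table 3 (D0), so that the covariate is a pre-feeding value.
2. In {20a}, for each of the three markers, make the arm comparison an ANCOVA of the day-5 value on arm and the baseline value. Report the adjusted mean difference with its 95% confidence interval. Use a transformed or rank scale if the distribution is clearly non-normal, which keeps a counterpart to the present rank-test option.
3. Report the paired within-patient change as description only, without a significance test.

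No further covariate is needed; the article states no stratification factor that would call for one.

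The cost is a sentence or two in the analysis section plus the timing correction, since both measurements are already scheduled. The downside is small: a model assumption replaces a simple two-sample test. Day-5 values missing through death or discharge remain a limitation under either analysis. The article plans no routine imputation, so the number of patients analyzed per arm should be shown with each estimate.

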## Data collection and management

### Plans for assessment and collection of outcomes {18a}

#### Demographic and baseline data

The study will collect demographic and baseline characteristics from medical records and electronic medical records, including age, sex, type of admission, and baseline characteristics. Patient weight will be measured on admission in a standard manner by using a bed-integrated scale; patient height will be measured on admission through a standardized protocol with a tape measure. The patient will lie flat in a supine position. A tape measure will be placed perpendicular to the patient, and the distance from the patient’s heels to the head will be measured.

Conventional scoring systems validated for critically ill patients will be used. Estimation of APACHE II, SOFA, and mNUTRIC scores will be performed by the attending physician and documented in the medical records. Results of laboratory tests will be documented in the electronic medical records and entered by the trial investigator in the eCRF.

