### Methods for additional analyses (e.g., subgroup analyses) {20b}

Not applicable.

Additional analysis is not planned.

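### 28-day mortality has no named comparison between the arms; a risk difference adjusted for the APACHE II and SOFA scores already collected would be clearer and modestly more precise

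*Protocol article*

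**What the plan says.** Mortality at 28 days is the last secondary outcome listed in the protocol article. Outcomes {12} says: "The 28-day mortality will be evaluated with a Kaplan-Meier curve". Statistical methods {20a} says: "A Kaplan-Meier curve will be used to demonstrate 28-day mortality". The same section names candidate tests for the primary outcome but none specifically for mortality.

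{20a} also has a general rule: "Secondary outcome measures will be compared between study groups" by a t test or Mann-Whitney test, and "the chi-square test will be used for categorical data". It adds that "Confidence intervals will be presented as appropriate", without naming an effect measure. Section {20b}, on subgroup and other further analyses, states: "Additional analysis is not planned".

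On the data, {18a} says of the severity scores: "Estimation of APACHE II, SOFA, and mNUTRIC scores will be performed by the attending physician and documented in the medical records". Table 3 puts allocation at screening, APACHE II and SOFA at D0, and the start of enteral nutrition at D1. Vital status at day 28 is obtained by telephone as alive or dead.

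**The concern.** Mortality is the most serious outcome the trial will report, and 300 patients is a small number for it. As written, the result could be a curve alone, a chi-square test on day-28 status, or a comparison of curves. None of these would use baseline severity, although two severity scores are already scheduled for every participant.

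If the scores predict death, leaving them out gives a wider confidence interval than the data allow. If the comparison is settled only after the data are seen, in an open-label trial, the mortality result carries less weight than one fixed beforehand.

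**Working it through.** **The plan's own figure.** There is none for mortality. The 122 per arm in Sample size {14} concerns time to the energetic target and has no bearing here. The article gives neither an expected mortality nor the prognostic strength of the scores, so both are assumed below and varied.

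**Inputs.** 150 patients per arm ({14}) and 1:1 allocation ({16a}). Assumed: 35% mortality overall, and a logistic relation between death and one standardised severity score.

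**Step 1, unadjusted standard error (SE) of the risk difference.**
SE = √(2 × 0.35 × 0.65 / 150) = √0.003033 = 0.055, or 5.5 percentage points.

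**Step 2, adjusted SE.** If the score explains a share R² of the outcome variance, the adjusted SE is about 5.51 × √(1 − R²). The equivalent gain in sample size is 1/(1 − R²) − 1.

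| Log-odds slope per SD | AUC for death | R² | Adjusted SE (points) | Equivalent extra patients |
|---|---|---|---|---|
| 0.40 | 0.61 | 0.034 | 5.4 | 4% |
| 0.75 | 0.69 | 0.105 | 5.2 | 12% |
| 1.00 | 0.74 | 0.165 | 5.0 | 20% |
| 1.20 | 0.77 | 0.213 | 4.9 | 27% |

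At an assumed 20% mortality, the last three slopes are worth 9% to 22% more patients.

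**Step 3, what this means for power.** Assume 30% v 20% mortality with 150 per arm. The unadjusted chi-square test has 51.6% power. With R² of 0.05, 0.10 and 0.20, power becomes 53.7%, 55.9% and 60.9%.

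**Step 4, check by simulation.** 300 patients, 30% v 20% mortality, chi-square test against logistic adjustment:

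| AUC | Power, chi-square | Power, adjusted | SD of risk difference, unadjusted | SD, standardised |
|---|---|---|---|---|
| 0.50 | 53% | 52% | 0.048 | 0.048 |
| 0.61 | 51% | 52% | 0.050 | 0.049 |
| 0.68 | 51% | 54% | 0.050 | 0.048 |
| 0.74 | 52% | 58% | 0.049 | 0.046 |

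The simulation agrees with the formula in direction and rough size. At AUC 0.74 the SE of the log odds ratio rises with adjustment, from 0.273 to 0.299, because the conditional odds ratio is a different quantity. The gain in precision appears on the risk-difference scale, so the effect measure has to be specified as well as the covariates.

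**The case against.** The strongest reply is that nothing here is an error. The trial is described as explorative, mortality does not appear among its stated objectives, and an unadjusted comparison in a randomised trial is valid. Covariates are often left to an analysis plan, which is not shown, and the {20b} sentence stands under a heading on subgroup and other further analyses, so it does not clearly settle them. All this stands, and it makes the point an improvement rather than a correction. It does not remove the ambiguity: the article chooses tests for other outcomes and gives mortality only a curve.

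Some stronger readings are tempting but not supported:

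- **Mortality will not be compared at all.** The general rule in {20a} covers secondary outcomes and can reach day-28 status. The comparison is unclear, not excluded.
- **Randomisation is unstratified, so severity imbalance biases the result.** The article describes 1:1 block randomisation and is silent on strata; silence in a condensed article does not show there are none. Chance imbalance is also not bias. A one-SE imbalance in severity would shift the mortality difference by √R² × 5.5, or 1.8 to 2.5 points for R² of 0.105 to 0.213, but the unadjusted SE already includes this.
- **Adjustment is free precision.** The gain is close to nil if the scores predict weakly, and the mNUTRIC entry threshold may narrow the severity range.
- **The same covariates should be used for ventilator-associated pneumonia and the other binary outcomes.** Nothing in the article shows that the scores predict these. For a rarer outcome (10% v 5%) and a weak covariate (AUC 0.61), the simulation finds no gain: 36% power unadjusted, 35% adjusted.

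A further caution stands. Table 3 places the scores after allocation, and unblinded attending physicians record them. Being scored before feeding is not the same as being scored before randomisation.

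**Conclusion.** The point holds as a modest, optional improvement confined to 28-day mortality. The article does not say how the arms will be compared on this outcome, and it makes no inferential use of the APACHE II and SOFA scores it collects. The unadjusted analysis is valid but may be less precise than it need be.

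Under the assumptions of 35% mortality and 150 analysed per arm, adjustment lowers the SE from 5.5 points to between 5.2 and 4.9 for an AUC of 0.69 to 0.77, a reduction of about 5% to 11%. At an AUC of 0.61 it lowers it only to 5.4. Neither the mortality nor the AUC comes from the documents. Naming the comparison in advance is worthwhile even if the precision gain proves small.

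**What to change.** In {20a}, state one mortality analysis:

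- Compare day-28 status by a standardised risk difference with 95% CI, from a logistic model with arm, APACHE II and SOFA as continuous terms.
- Require both scores to be based on data from before randomisation.
- Report the unadjusted risk difference beside it.
- Keep the Kaplan-Meier curve as display.

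The cost is a sentence or two and a standard model. The scores are already scheduled, and the alive-or-dead status obtained at day 28 is the outcome the model needs. There is one small downside: {20c} plans no imputation, so a patient with a missing score would drop out of the adjusted model while remaining in the unadjusted comparison. A simple rule for missing baseline scores, fixed in advance and blind to arm and outcome (for example the overall mean with a missingness indicator), keeps every patient in.
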